### Outcome

The outcome of interest is incident central retinal artery occlusion. Central retinal artery occlusion will be identified through ICD-9-CM 362.31, which we validated in a prior study [13] in the primary diagnosis position in any emergency department, inpatient, or outpatient claim. We will use the corresponding ICD-10-CM code H34.1x for claims occurring after September 31, 2015.

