### Sample size calculation

Power/sample size calculations were made on the basis of an unadjusted Cox proportional hazards regression model. Within the primary analysis of aim 1, assuming a loss to follow-up of 20%, 570,000 subjects (285,000 with AF and 285,000 without) would have 90% power to detect a hazard ratio of 2, at an alpha of 0.05. This conservatively assumes an event rate of 22/100,000 per year in the exposed group (a rate of 45/100,000 is reported previously) [10] and an event rate of 11/100,000 per year in the unexposed group (a rate comparable to that reported previously) [15]. A query of the Medicare 5% sample between 2000 and 2015 reveals 818,940 unique patients with AF and 11,400 unique patients with a new diagnosis of CRAO. Power calculations were performed with the *powerSurvEpi* package (R v4.0.3).

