### Inclusion and exclusion criteria (Aim 1)

The inclusion criterion is continuous fee-for-service Medicare enrollment for at least 12 months prior to AF diagnosis or matched index date (July 1 of inclusion year) for controls and continuous enrollment in fee-for-service (FFS) Medicare after AF diagnosis/index date for at least 12 months or until death if death occurred before 12 months of continuous enrollment.

Patients with prevalent AF will be identified as follows:ICD-9-CM code 427.31 or ICD-10-CM code I48 in 2 outpatient claims or 1 inpatient claim within 365 days, in any diagnosis position of the claim [16–18]. The index date will be the date of the first qualifying inpatient claim or second qualifying outpatient claim. Patients will be required to have 12 months of FFS claims without an AF diagnosis prior to the index AF claims based on inclusion criteria.

Exclusion criteria are:

patients with any claim for CRAO in the 12 months prior to AF diagnosis or index date for controls (July 1 of potential inclusion year).

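### The 12-month clean window and the any-setting, single-claim outcome allow an old CRAO to count as incident, and the protocol's statements of the prior-CRAO exclusion conflict

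*Protocol article*

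**What the plan says.** All references are to the protocol article.

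- **Outcome:** "The outcome of interest is incident central retinal artery occlusion". It is identified by the CRAO code "in the primary diagnosis position in any emergency department, inpatient, or outpatient claim". No second claim or acute setting is required. The section says the ICD-9 code was validated in the investigators' earlier study.
- **Inclusion and exclusion criteria (Aim 1):** excluded are "patients with any claim for CRAO in the 12 months prior to AF diagnosis or index date for controls". The Aim 2 criteria repeat this rule.
- **Inclusion and exclusion criteria (Aim 2):** for the exposed group the index date is the first anticoagulant claim after AF diagnosis, but the CRAO window still runs back from AF diagnosis.
- **Regression modeling (aim 2), item b:** said to be similar to Aim 1, this excludes CRAO before or at AF diagnosis with no time limit and sends those patients to an exploratory analysis.
- **Regression modeling (aim 1), item h:** one outcome sensitivity analysis accepts the code in any diagnosis position; the other accepts any retinal artery occlusion.
- **Sample size calculation:** "an event rate of 11/100,000 per year in the unexposed group" and "an event rate of 22/100,000 per year in the exposed group".

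**The concern.** Aim 1 asks whether AF precedes and predicts CRAO, so the order of the two must be secure. An outpatient claim with CRAO as its primary diagnosis may record a new occlusion or a visit for an old one, and the outcome rule does not separate them. Only the clean window does, and 12 months is all that the criteria require. A patient whose CRAO was three years before index, with no CRAO code in the last year, passes the exclusion. That patient's next visit with the code in primary position is then dated as a new event after index.

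If this happens equally in both arms it pulls the hazard ratio toward 1. If it happens unequally it can move the ratio either way. Because the protocol describes the prior-CRAO exclusion in two incompatible ways, the arms could also end up with different exclusions depending on which text the programmer follows.

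**Working it through.** **1. The passages side by side**

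| Group | Eligibility criteria | Aim 2 modeling, item b | What remains |
|---|---|---|---|
| Aim 1, AF | 12 months before AF diagnosis | any CRAO before or at AF diagnosis (by its reference to Aim 1) | conflict |
| Aim 1, controls | 12 months before 1 July index | not covered: no AF diagnosis | CRAO older than 12 months |
| Aim 2, exposed | 12 months before AF diagnosis | any CRAO before or at AF diagnosis | conflict; CRAO between AF diagnosis and first anticoagulant claim |
| Aim 2, controls | 12 months before index | any CRAO before or at AF diagnosis | conflict; CRAO after AF diagnosis but more than 12 months before index |

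For the Aim 2 exposed group the gap needs no quiet year. A CRAO shortly before the first anticoagulant claim is not excluded, and a later visit for it falls after index.

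**2. Would another part of the plan catch the error?**

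- Validation: Prior work addressing this question says the earlier study used hospitalizations and emergency visits and had no outpatient data. It cannot speak for outpatient claims.
- Claim rule: AF needs two outpatient claims or one inpatient claim (Exposure). CRAO needs one claim of any kind.
- Control endpoints: ischemic stroke and urinary tract infection are both restricted to hospital or ED claims, so they do not test the any-setting rule.
- Outcome sensitivity analyses: both widen the definition; neither lengthens the window or restricts the setting.
- Weighting: prior CRAO is not among the listed covariates, so overlap weighting does not balance it.

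**3. The plan's own figure**

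Inputs: "570,000 subjects (285,000 with AF and 285,000 without" AF), which "would have 90% power to detect a hazard ratio of 2, at an alpha of 0.05"; rates 22 and 11 per 100,000 per year; 20% loss. Follow-up length is not stated; one year is assumed because the rates are per year.

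- Freedman events, two-sided: [(2+1)/(2−1)]² × (1.960+1.282)² = 94.6, so 95.
- Mean rate 16.5 per 100,000: N = 95/0.000165 = 575,758, close to 570,000. This is before any allowance for loss.
- With 20% loss, 456,000 are retained: 75.2 events, two-sided power 82%. One-sided power is 89%.

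So 570,000 is reproduced two-sided without the loss, or one-sided with it. That is a separate matter; the present point needs only the two rates.

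**4. Possible size**

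The documents do not give the number of survivors of an old CRAO or how often they are recoded after a gap. Assume 5–10 years of surviving past cases and a yearly recoding share s of 5% (range 2–10%).

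- Old cases in the unexposed: 11 × 5 = 55 to 11 × 10 = 110 per 100,000.
- False rate c = old cases × s.
- Share of counted unexposed events = c/(11+c).
- Apparent HR when c is added to both arms = (22+c)/(11+c).

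| s | c per 100,000/yr | Share of unexposed events | Apparent HR (true HR 2) |
|---|---|---|---|
| 2% | 1.1–2.2 | 9–17% | 1.91–1.83 |
| 5% | 2.75–5.5 | 20–33% | 1.80–1.67 |
| 10% | 5.5–11 | 33–50% | 1.67–1.50 |

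At 5%, on the one-year, 456,000-subject, two-sided Freedman basis, power falls from 82% to 76% (HR 1.80, 87.8 events) or 71% (HR 1.67, 100.3 events).

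**5. Direction**

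With false rates c₁ (AF) and c₀ (no AF), the apparent HR is (22+c₁)/(11+c₀), a weighted average of the true HR and c₁/c₀. At 5%:

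- Old CRAO twice as common in the AF arm, true HR 1: (11+5.5)/(11+2.75) = 1.20 to (11+11)/(11+5.5) = 1.33. With a true HR of 2 the same excess leaves it at 2.
- Old CRAO left only among controls (item b applied to AF patients alone), true HR 2: 22/13.75 = 1.60 to 22/16.5 = 1.33.

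**The case against.** **The window is stricter than it looks.** It removes any CRAO claim, not only primary-position ones, so a patient with regular coded eye visits is already excluded. Misclassification needs an old CRAO, then a year with no CRAO code, then a primary-position code. This stands and limits the size. Repeat visits after a first counted event also do no harm in a time-to-first-event model.

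**Continuing visits are not documented.** A reader might infer that CRAO leaves lasting loss with years of eye visits, so that old occlusions do count as new events. The protocol says only that the visual loss is severe and disabling. The text supports that they can count, not that they do or how often.

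**The bias might not favor AF.** A reader might infer a spuriously raised hazard ratio from Regression modeling (aim 1), item i, which hypothesizes that undetected AF may be associated with CRAO. But the Aim 2 item b wording would remove earlier CRAO from AF patients and leave it among Aim 1 controls, which lowers the ratio. The direction is not established.

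**A larger size is tempting.** Using the 45 per 100,000 rate gives 45 × 10 × 5% = 22.5, twice the unexposed rate of 11. However, 45 is a previously reported rate for the exposed group, so it is not a like-for-like comparison.

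**Unlimited look-back has its own flaw.** Only 12 months of prior claims are guaranteed. AF patients are indexed at diagnosis and controls in a randomly chosen eligible year, so available history may differ between arms. A fixed, equal window is a defensible choice. This stands, and is why a fixed-window analysis belongs beside any longer look-back.

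**Conclusion.** The concern holds in a limited form. The outcome and exclusion rules together let an old CRAO with a 12-month coding gap count as incident, and nothing else described in the article would reveal it. The eligibility criteria and Regression modeling (aim 2), item b, state different exclusions. The Aim 2 exposed group is cleared to the wrong date for its own index. These are conflicts within the article, not details left to a fuller document.

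The size is conditional. On 5–10 years of surviving cases and 5% yearly recoding, 2.75–5.5 false events per 100,000 per year would be added to the unexposed rate of 11 (1.1–2.2 at 2%, 5.5–11 at 10%). Equal addition takes a true HR of 2 to about 1.80–1.67. Neither the recoding share nor the number of survivors comes from the documents. The one count given, 11,400 new CRAO diagnoses in 2000–2015 or about 712 a year, cannot settle it, because the size of the 5% sample is not stated.

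**What to change.** 1. Replace the three statements (Aim 1 criteria, Aim 2 criteria, and item b of the Aim 2 modeling) with one prior-CRAO exclusion. Apply it identically to both groups and tie it to each group's own index date, including the first anticoagulant claim in Aim 2. Use all earlier claims available, with 12 months as the minimum.
2. Add a sensitivity analysis with a fixed, longer CRAO-free window, equal in both arms, for example 36 months of fee-for-service claims.
3. Add a sensitivity analysis that counts CRAO only when the patient's earliest CRAO code comes from an ED visit or inpatient stay.

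No new data are needed: the source follows beneficiaries over 2000–2020 while they remain in fee-for-service. The cost is some programming and the loss of some patients and events in the two sensitivity analyses; the third item also drops true occlusions first seen in outpatient care. Available look-back will vary by entry year and may differ between arms, and the fixed-window analysis checks for that.

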### Adjustment covariates

We will utilize the following pre-specified covariates for risk adjustment: age, biological sex, race/ethnicity, and cardiovascular comorbidities and medical risk factors, including the medical comorbidities included in the Charlson Comorbidity Index (except for cardiac arrhythmias, which subsumes our primary exposure of interest), and additionally including hypertension, hyperlipidemia, valvular heart disease, and smoking status, using validated ICD-9-CM and ICD-10-CM algorithms [20–23]. Carotid stenosis and Stroke/TIA are contained in the cerebrovascular disease group of the Charlson Comorbidity Index. S1 and S2 Figs show the directional acyclic graphs representing our understanding of possible confounding variables.

We will ascertain comorbidities using a twelve-month look-back period from the patient’s index date (July 1 of initial year of inclusion in cohort for controls) using established claims-based algorithms. These are outlined in Table 2, below.

**Table 2 pone.0296251.t002:** List of international classification of diseases codes used for comorbidity adjustment.

Comorbidity	ICD-9 Code	ICD-10 Code	Citation
Hypertension	401.*, 402.*, 403.*, 404.*, 405.*, 437.2*	I10.*-I13.*, I15.0, I15.2, I15.8, I15.9, I16.*, I67.4*	Birman-Deych, 2005 [21]
Hyperlipidemia†	272.x	E78.x	Oake, 2017 [22]
Tobacco Use††	305.1, 649.0x, 989.84, V15.82; CPT codes 99406, 99407, G0436, G0437, G9016, S9453, S4995, G9276, G9458, 1034 F 4004 F 4001 F	F17.x, T65.2xx, Z87.891, CPT codes 99406, 99407, G0436, G0437, G9016, S9453, S4995, G9276, G9458, 1034 F 4004 F 4001 F	Desai, 2016 [23]
Valvular Heart Disease	394.*, 395.*, 396.*, 397.*, 398.9*, V42.2*, V43.3*, 424.*	I05.*-I08.*, I09.1*, I09.81, I09.89, I09.9*, I34.*-I39.*, Z95.2*, Z95.3*, Z95.4*	Birman-Deych, 2005 [21]

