#### Regression modeling (aim 1)

a) The study index date will be the date of the first AF claim in the study and July 1 in the first year of inclusion in the analytic cohort for controls for the purposes of our survival analysis.b) We will describe cumulative incidence of CRAO over time with the overlap-weighted cumulative incidence function and presented graphically for patients with and without atrial fibrillation. Next, a weighted, unadjusted cause-specific hazard model will be fit with AF as the univariable predictor and CRAO as the event of interest, with patients censored at death, at end of data availability, or at end of fee-for-service Medicare enrollment.c) Then, a weighted cause-specific hazard model, clustered by state, and adjusting for age, sex, race, cardiovascular comorbidities will be fitted. Directly adjusted cumulative incidence curves for AF and control patients will be created with adjustment for all model covariates [28].d) We will test the proportional hazards assumption for all models.e) Our primary analytical model will be an overlap-weighted model with propensity scores derived from the adjustment covariates previously described as predictors for the presence of atrial fibrillation. We will report our results with sequential adjustment to produce the fully-adjusted, weighted model. We employ this sequential adjustment strategy to provide insight as to sources of measured confounding.f) We will evaluate **positive control endpoints**. Our positive control endpoints will be any ischemic stroke (defined by ICD-9-CM 434.0, 434.00, 434.10, 434.11, 434.9, 434.90, 434.91, 436/ ICD-10-CM I66.09, I66.19, I66.29, I66.9, I63.40, I63.50, I67.89 in the primary diagnosis position in a hospitalization or ED visit) [29]. We will utilize the same modeling strategy as used for the primary outcome.g) We will evaluate **negative control (falsification) endpoints**. Our negative control endpoint will be hospitalized/ED urinary tract infection (including renal abscess and pyelonephritis) (ICD-9-CM 590.1, 590.11 590.2, 590.8 or 599.0/ ICD-10-CM N15.1, N39.0, N10). We will utilize the same modeling strategy as used for the primary outcome [30].h) We will perform several sensitivity analyses for outcome ascertainment.

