#### Regression modeling (aim 2)

a) In keeping with target trial emulation methodology as described above, the index date for patients exposed to anticoagulation will be the date of the first anticoagulant prescription drug claim occurring after the diagnosis of AF. For potential controls, only patients with no exposure to anticoagulation throughout the study period would be eligible to avoid selecting controls who start an anticoagulant during the follow-up period. For controls, inclusion and exclusion criteria will be examined for each year after AF diagnosis, and the midpoint of one random year will be selected as the index date for each control patient.b) Similar to Aim 1, patients diagnosed with CRAO precedent to or concurrent to AF diagnosis will be excluded and these patients will be examined in an exploratory analysis.c) Our primary analysis will utilize propensity score overlap weighting methodology to approximate a randomized design where baseline hazard of CRAO of patients receiving anticoagulation vs. not receiving is comparable. We will incorporate the following variables to define the propensity score: age, time since first AF claim, sex, geography, race, Medicaid dual eligibility, vascular comorbidities and non-vascular comorbidities relevant to the likelihood that a patient will be treated with anticoagulation (to include all of the comorbidity variables included for Aim 1 propensity score, as well as history of gastrointestinal bleeding or peptic ulcer disease (using validated ICD-9-CM codes 531.x (gastric ulcer), 532.x (duodenal ulcer), and 578.x (gastrointestinal hemorrhage) and their ICD-10-CM counterparts K25.x, K26.x, and K92.2) and history of intracranial hemorrhage (any of ICD-10-CM I60, I61, S06.3, S06.4, S06.5, S06.6 and their ICD-9-CM counterparts 430.x, 431.x, 432.x)) [32–35].d) Our principal effect of interest is the hazard of CRAO among patients treated with any oral anticoagulant agent compared to those not treated. Given variable patient adherence to anticoagulation, we will take advantage of the strength of Part D data (which records pharmaceutical fills rather than prescriptions) and treat anticoagulation exposure as a time-varying covariate for patients exposed to anticoagulation.e) We will perform identical sensitivity analyses as described in Aim 1.f) Table shells for the results of Aim 2 are shown in Table 8.

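### The Aim 1 adjustment set omits geography and Medicaid dual eligibility, both of which are in the Aim 2 propensity score; clustering by state does not stand in for them

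*Protocol article*

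**What the plan says.** **Aim 1.** The Adjustment covariates section opens its list with "We will utilize the following pre-specified covariates for risk adjustment: age, biological sex, race/ethnicity". It then takes in the Charlson conditions, "additionally including hypertension, hyperlipidemia, valvular heart disease, and smoking status". Regression modeling (aim 1), item e, makes the primary model an overlap-weighted one with "propensity scores derived from the adjustment covariates previously described as predictors for the presence of atrial fibrillation". Item c describes the outcome model as "clustered by state, and adjusting for age, sex, race, cardiovascular comorbidities will be fitted". None of these places names geography or Medicaid dual eligibility as a covariate.

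**Aim 2.** Regression modeling (aim 2), item c, begins its propensity-score list with "age, time since first AF claim, sex, geography, race, Medicaid dual eligibility" and goes on to comorbidities and bleeding history. From the Aim 1 score it imports only the comorbidity variables. Geography and dual eligibility are named separately and are not attributed to Aim 1.

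The visible text gives no reason for the difference. It refers to causal graphs in S1 and S2 Figs, which are not reproduced in the text at hand.

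**The concern.** The first aim asks whether AF is a risk factor for CRAO in its own right. Exposure and outcome are both defined by claims codes, so both depend on whether a patient reaches care and how that care is coded. Income-related access and regional coding habits could therefore influence recorded AF and recorded CRAO together. The Introduction itself attributes shortcomings of earlier work to incomplete adjustment in one study and to under-ascertainment of both AF and CRAO in another.

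Two features of the plan might look as though they deal with this. One is the state clustering in the Aim 1 model. The other is the exact covariate balance that the overlap-weighting section promises, but that balance covers only variables entered in the propensity model. The Table 2 footnotes also concede that claims identify smoking and hyperlipidemia with poor sensitivity, so socioeconomic status could carry some of the confounding that those variables miss.

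At stake is some avoidable residual confounding in the primary hazard ratio. It would matter most if that ratio turned out close to 1.

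**Working it through.** The plan states no figure on this point, so there is none to reproduce. The check has three parts.

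**1. The lists side by side**

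| Variable | Aim 1 propensity score | Aim 1 outcome model | Aim 2 propensity score |
|---|---|---|---|
| Age, sex, race | yes | yes | yes |
| Comorbidities | yes | cardiovascular | yes, plus bleeding history |
| Geography | no | state, for clustering only | yes |
| Medicaid dual eligibility | no | no | yes |

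Table 3, the Aim 1 baseline shell, has no row for geography or dual eligibility. Table 4, the Aim 2 shell, has none either, so the shells do not settle the matter. The text lists do.

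**2. What clustering does**

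The wording of item c keeps "clustered by state" apart from the adjustment terms. To show the mechanism, a log-linear rate model was simulated with 50 states, a true exposure rate ratio of 2.0, and confounding by state and dual status of assumed strength:

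| Analysis | Rate ratio | SE of log rate ratio |
|---|---|---|
| Exposure only, ordinary SE | 2.474 | 0.021 |
| Exposure only, state-clustered SE | 2.474 | 0.032 |
| State and dual status as covariates | 2.03 | 0.021 |

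Clustering leaves the confounded estimate where it was and changes only its standard error. Entering the variables as covariates brings the estimate back close to the truth. The confounding strengths were invented, so the gap between 2.47 and 2.03 says nothing about the size to expect in this study.

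**3. Size of the bias from dual status alone**

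For an omitted binary confounder with prevalence p1 in AF, p0 in non-AF and rate ratio r for CRAO:

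bias factor = [1 + p1(r − 1)] / [1 + p0(r − 1)]

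The documents give none of these inputs, so all are assumptions.

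- p1 = 0.20, p0 = 0.15, r = 1.3: 1.060 / 1.045 = 1.014
- p1 = 0.25, p0 = 0.15, r = 1.5: 1.125 / 1.075 = 1.047
- Reversed, p1 = 0.15, p0 = 0.20, r = 1.3: 1.045 / 1.060 = 0.986
- Reversed, p1 = 0.15, p0 = 0.25, r = 1.5: 1.075 / 1.125 = 0.956
- A more extreme case, p1 = 0.30, p0 = 0.15, r = 2.0: 1.30 / 1.15 = 1.130

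Leaving the extreme case aside, a true hazard ratio of 2 would be estimated between 2 × 0.956 = 1.91 and 2 × 1.047 = 2.09. A true hazard ratio of 1 would be estimated between 0.96 and 1.05. No calculation was made for geography.

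**The case against.** A reader who sets the two lists together might infer that the protocol contradicts itself. It does not. One score models having an AF diagnosis and the other models receiving an anticoagulant, and confounder sets need not match across exposures. Payment status and local practice bear plausibly on filling a prescription, so their presence in Aim 2 does not show that the authors regard them as confounders of AF and CRAO. The causal graphs may explain the difference and cannot be checked here. This objection stands in full against any charge of inconsistency.

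The size is also open to challenge. Every input is assumed. The comparison is made after matching and weighting on race, smoking recorded in claims and many comorbidities, some of which probably correlate with dual status, so the remaining imbalance may be smaller than assumed. Even its direction is unknown. This stands too.

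The plan is not blind to residual confounding. It has a urinary tract infection falsification endpoint and an ischemic stroke positive control, and its Limitations section acknowledges the problem. These can reveal bias of this kind but cannot remove it.

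Finally, if state were fitted as a stratum or frailty term, geography would be partly handled in that one model. Dual eligibility would still not be.

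**Conclusion.** The point holds as an optional improvement to the choice of covariates. The Aim 1 score and outcome model leave out two baseline variables that the same plan uses in Aim 2, and state clustering, read in the usual way, does not balance them. Some avoidable residual confounding may remain in the primary hazard ratio.

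Under the assumed prevalences and rate ratios, the factor from dual status is about 1.01-1.05 in one direction and about 0.96-0.99 in the other. That would not overturn a hazard ratio near the design value of 2. It could colour the reading of an estimate near 1, which is a realistic prospect because the Introduction reports an inverse association in the team's own earlier study.

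A reader might go further and conclude that the primary hazard ratio is biased upward. The documents do not support that, since they give neither the imbalance nor the effect of either variable on CRAO.

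**What to change.** Add Medicaid dual eligibility and state, or census region, to the Aim 1 propensity model used for matching and to the score re-estimated for overlap weighting. Keep the clustering by state for the variance. If the Aim 1 causal graph deliberately excludes either variable, say so and give the reason.

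The cost is low but not zero. State is already needed for Aim 1 because the model clusters on it. Dual status is different: the Aim 2 cohort holds only AF patients with Part A, B and D enrollment, so extraction for Aim 2 does not cover the non-AF controls or AF patients without Part D. It would have to be pulled for the whole Aim 1 cohort. That it is obtainable there is a reasonable inference from the shared Medicare source, not something the protocol states. The score also gains terms: a few with census region, more with individual states, and easily carried by the planned 570,000 subjects.
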